# Effects of vitamin D and omega-3 fatty acids co-supplementation on inflammatory biomarkers, tumor marker CEA, and nutritional status in patients with colorectal cancer: a study protocol for a double blind randomized controlled trial

**DOI:** 10.1186/s13063-019-3719-3

**Published:** 2019-12-09

**Keywords:** Vitamin D, Omega-3 fatty acids, Colorectal cancer, Inflammatory biomarkers, Tumor marker CEA, Nutritional status

## Abstract

**Background:**

Much evidence is available demonstrating that both vitamin D and omega-3 fatty acids block the development and progression of colonic carcinogenesis. The results of animal studies have shown that the consumption of omega-3 fatty acids can decrease inflammatory biomarkers, enhance the efficacy of chemotherapy, and decrease the side effects of chemotherapy or cancer. Also, observational studies propose that higher levels of 25(OH)D are related to improved survival of colorectal cancer patients. This study will aim to evaluate the effects of vitamin D and omega-3 fatty acids co-supplementation on inflammatory biomarkers, tumor marker CEA, and nutritional status in colorectal cancer patients.

**Methods/design:**

We will carry out an 8-week double-blind randomized, placebo-controlled clinical trial to evaluate the effects of vitamin D and omega-3 fatty acids co-supplementation on inflammatory biomarkers, tumor marker CEA, and nutritional status in patients with stage ӀӀ or ӀӀӀ colorectal cancer undergoing chemotherapy.

**Discussion:**

Because of the important effects of vitamin D and omega-3 fatty acids on molecular pathways involved in cancer development and progression, it seems that both vitamin D and omega-3 fatty acids may provide a new adjuvant therapy by decreasing inflammatory biomarkers and resistance to cancer treatment in patients with colorectal cancer.

**Trial registration:**

Iranian Registry of Clinical Trials IRCT20180306038979N1. Registered on 16 March 2018.

## Background

Colorectal cancer (CRC) is an important public health problem and comprises a significant proportion of the global cancer burden with regard to morbidity and mortality. Epidemiological studies have demonstrated that CRC is the third most common cancer in the world [1], and it is ranked fourth in terms of deaths from cancer worldwide according to the World Health Organization [2]. Development of CRC is a multistep process including epigenetic and genetic changes that disturb cell homeostasis between cellular proliferation and apoptosis [1]. In colonic tumorigenesis, inflammatory cells lead to colitis by generating inflammatory factors and a variety of reactive oxygen species (ROS) and reactive nitrogen species (RNS). Oxidative stress impacts a large range of carcinogenic pathways because of its effects on DNA, RNA, proteins, and lipids, contributing to the progression of malignant transformation and proliferation of initiated cells [3]. Inflammation also enhances cancer progression by generating an inflammatory environment during tumor formation. The inflammatory and immunosuppressive agents released from these cells not only increase proliferation, angiogenesis, invasion, and metastasis, but also repress the host’s immune system and accelerate tumor growth and development of CRC [3]. Various molecular alterations occur during the development of CRC, including those involved in cell proliferation, cell survival, differentiation, resistance to apoptosis, metastasis, and tumor angiogenesis [4, 5].

It has been indicated that absolute carcinoembryonic antigen (CEA) level is an independent prognostic marker for CRC patients and may demonstrate tumor biological activity [6].

Throughout colonic carcinogenesis, particular molecular processes have been targeted for chemopreventive intervention, including chronic inflammation, proliferation, differentiation signaling, apoptosis, cell surface growth factor receptors, angiogenesis, and metastasis [3]. Despite understanding the pathway and mechanism of colon tumor progression, current therapies, including surgery, chemotherapy, radiotherapy, and molecular-targeted therapy, are still limited for some tumors [3]. Hence, a growing amount of scientific attention has been concentrated on evaluating the potential of dietary components for both prevention and control of CRC.

Among dietary components, a growing number of epidemiological, clinical, and experimental studies propose a protective impact of n-3 polyunsaturated fatty acids (PUFA; found in fish oil) on CRC [5, 7, 8]. Investigations with fish oil, which contains eicosapantaenoic acid (EPA; C20, omega-3) and docosahexaenoic acid (DHA; C22, omega-3), have demonstrated a protective impact against the induction and progression of experimentally generated colon cancer in an animal model [7]. Molecular mechanisms suggested to contribute to the multiple advantages of omega-3 fatty acids include: 1) suppression of the expression of cyclooxygenase-2 in malignant cells, thus reducing proliferation of these cells and consequently decreasing angiogenesis in them; 2) reduction of expression of AP-1 and ras, two oncogenes involved in tumor progression; 3) induction of differentiation in malignant cells; 4) repression of nuclear factor kappa-B (NF-kB) and bcl-2 expression, hence allowing apoptosis of cancer cells; and 5) decreased cancer-induced cachexia [8]. Moreover, dietary DHA significantly weakened the growth of human colon carcinoma WiDr in athymic mice containing mutated P53 [7]. The results of animal studies have shown that the intake of omega-3 fatty acids can slow the growth of cancer xenografts, promotes the efficacy of chemotherapy, and decreases the side effects of the cancer or of chemotherapy [7]. Therefore, it appears reasonable to consider that, along with cancer therapy, consumption of omega-3 fatty acids might reduce or stop the growth of metastatic malignant cells, enhance longevity of cancer patients, and improve their quality of life.

Several other reports have also demonstrated positive impacts of combining vitamin D or its analogues with a variety of chemotherapeutic factors in the treatment of various cancers [9–11]. Recently, supplementation with vitamin D analogues has been indicated to enhance the sensitivity of colon cancer cells to 5-fluorouacil and to increase the cytotoxic impacts of the drug both in vitro and in vivo [12–15]. The vitamin D receptor is present not only in cells and tissues involved in calcium regulation but also a large variety of other cells consisting of malignant cells [16]. Binding of vitamin D receptor by 1,25(OH)_2_D results in multiple cellular effects, including induction of differentiation and apoptosis and inhibition of proliferation, angiogenesis, and metastatic capability [17]. Remarkably, a relationship between the risk of developing cancer, latitude, low sun exposure, and low vitamin D has been reported [18]. Additional studies evaluating the relationship between serum 25(OH)D levels, dietary vitamin D intake, and cancer risk also observed a consistent reverse association between 25(OH)D concentration and CRC incidence [16, 17, 19]. Furthermore, the Women’s Health Initiative, a large randomized placebo controlled calcium/vitamin D trial, demonstrated that calcium plus vitamin D supplementation significantly reduced the risk of total, breast, and colorectal cancers [20]. Reverse relationships between serum 25(OH)D concentrations measured at diagnosis and subsequent CRC recurrence and mortality have also been reported [18]. On the other hand, the results of a nationwide, randomized, placebo-controlled trial of vitamin D_3_ (2000 IU per day) and marine omega-3 fatty acids (1 g per day) for the prevention of cancer and cardiovascular disease among men 50 years of age or older and women 55 years of age or older in the United States, demonstrated, during a median follow-up of 5.3 years, that supplementation with vitamin D or omega-3 fatty acids did not result in a lower incidence of invasive cancer than placebo [21, 22]. In addition, some meta-analyses looking at vitamin D and cancer incidence and mortality reported that vitamin D supplementation decreased the risk of cancer mortality [23, 24] but did not decrease total cancer incidence [24].

Given the importance of studying the role of vitamin D and omega-3 fatty acids as anticancer agents, and because the effect of co-supplementation with them on clinical outcomes of patients with CRC is not clear, the aim of this study is to evaluate the effects of vitamin D and omega-3 fatty acids co-supplementation on inflammatory biomarkers, tumor marker CEA, and nutritional status in patients with CRC.

## Methods/design

### Design

We will conduct an 8-week, double-blind randomized controlled trial in a factorial design. This trial will be conducted at the oncology clinic of Tehran Gastroenterology & Hepatology Center (TGHC), Iran for 8 weeks to evaluate the effects of vitamin D_3_ (50,000 IU weekly) and omega-3 fatty acids (660 mg daily) co-supplementation on inflammatory biomarkers, tumor marker CEA, and nutritional status in patients with CRC (Figs. 1 and 2). The protocol is written in line with the Standard Protocol Items: Recommendations for Interventional Trials (SPIRIT) checklist (Additional file 1).

**Fig. 1 Fig1:**
[figure not shown]
Protocol flow diagram; we will carry out an 8-week, double-blind, randomized controlled trial to determine the effects of vitamin D and omega-3 fatty acids co-supplementation on inflammatory biomarkers, tumor marker CEA, and nutritional status in patients with colorectal cancer

**Fig. 2 Fig2:**
[figure not shown]
Timeline of the study; we expect the duration of this trial will be 24 months

### Objectives and hypotheses of the study

The primary objective of the present study is to assess the impact of 8-week vitamin D_3_ and omega-3 fatty acids co-supplementation on serum 25(OH)D, inflammatory biomarkers, CRP/albumin, tumor marker CEA, body mass index (BMI), and body composition in patients with stage ӀӀ or ӀӀӀ CRC undergoing chemotherapy. As a second objective, the study will also evaluate the relationship between alterations in 25(OH)D levels and other variables. It is also expected that there will be improvement in evaluated variables.

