### Sample size

The number of participants was calculated according to the alterations in TNF-α between the control and co-supplementation groups and based on the study conducted by Mohammadzadeh et al. [25]. It was calculated with the use of fixed factor levels model (determining sample size for analysis of variance) [26] and considering sigma (standard deviation of TNF-α) of 1.25, 90% power, α of 0.05, resulting in 20 patients for each group. To allow for attrition, 25 patients will be recruited for each group. Collectively, a sample of 100 patients with stage II or III CRC will be enrolled.

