### Measurements

A questionnaire about patients’ medications, diseases, cancer history, and probable supplement use will be recorded at the beginning of the intervention. Dietary intake will be evaluated by 3-day, 24-h record questionnaires (two week days and one weekend day) at baseline and the end of the intervention, and total energy, macronutrient, and some micronutrient (vitamins A, D, E; calcium and selenium) intake will be estimated using nutritionist IV software. To evaluate physical activity levels the short form of the international physical activity questionnaire (IPAQ) [27] will be used at baseline and the end of the intervention. Sun exposure will be assessed with the questionnaire [28] at baseline and the end of the study. A sunshine exposure score is obtained based on (a) how often and what time of day the subjects are outside, (b) which parts of the body are exposed as a percentage of total body surface area, and (c) do the subjects use sun screen or not. Anthropometric indices will be measured after overnight fasting, with minimal clothing and without shoes, before and after the intervention. Body weight will be measured to an accuracy of 0.1 kg using a Beurer scale (Beurer, Germany). Height will be assessed to the nearest 0.5 cm in the standing position without shoes. BMI will be computed as body weight (kg) divided by height squared (cm^2^). A bioelectric impedance analyzer (Quad scan 4000; Body stat) will be used to measure total body fat and fat free mass percentage. The difference in CRP/albumin levels, as an indicator of nutritional status, between groups will also be compared with score values proposed by Correa et al.: no risk ≤ 0.4; low risk = 0.4–1.2; medium risk = 1.2–2; high risk ≥ 2.0 [29]. This indicator will be assessed at baseline and end of the intervention.

Before and after the intervention, blood samples will be collected after 12-h overnight fasting. The serum of patients will be kept at − 80 °C until biochemical analyses. Serum 25(OH)D will be measured by enzyme-linked immunosorbent assay (ELISA) and Euro Immun kit (Euro Immun, Germany). Serum TNF-α, IL-1β, IL-6, and IL-8 levels will be assessed by ELISA and Bender Med kit (Bender Med, Germany). Serum CRP and albumin will be determined by ELISA and Binding kit (Binding, UK). Tumor marker CEA will be evaluated by ELISA and CanAg kit (CanAg, Italy).

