### Statistical analysis

All analyses will be performed with STATA statistics software, version 11.0 (STATA Corporation, College Station, EUA). Kolmogorov-Smirnov test will be used to assess normality of data. Quantitative and normally distributed parameters will be expressed as mean + standard deviation. Quantitative and non-normally distributed data will be shown as median and interquartiles. Analysis of variance (ANOVA) test will be used for comparing the values between and within groups. Analysis of covariance (ANCOVA) will be used to identify any differences between the four groups at the end of study, adjusting for baseline values and covariates (such as dietary intake, physical activity, and sun exposure). Bonferroni will be used to pairwise comparisons for the values after the intervention.

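### The primary objective ranks none of its outcomes: TNF-α, the only one the trial is sized on, is not named primary, and 25(OH)D, a marker of uptake, is listed as primary

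*Protocol article*

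**What the plan says.** Objectives and hypotheses of the study sets a single primary objective, the effect of 8 weeks of "co-supplementation on serum 25(OH)D, inflammatory biomarkers, CRP/albumin, tumor marker CEA, body mass index (BMI), and body composition". No item is put ahead of another. The second objective only relates changes in 25(OH)D to the other variables, so every group comparison of an outcome sits in the primary tier.

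Measurements shows what the group terms contain. For the cytokines: "Serum TNF-α, IL-1β, IL-6, and IL-8 levels will be assessed by ELISA". For CRP: "Serum CRP and albumin will be determined by ELISA"; the same section uses CRP in the CRP/albumin ratio as an indicator of nutritional status. For body composition, an impedance analyzer "will be used to measure total body fat and fat free mass percentage".

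Sample size states that the number of participants was "calculated according to the alterations in TNF-α between the control and co-supplementation groups", "considering sigma (standard deviation of TNF-α) of 1.25", with "90% power, α of 0.05, resulting in 20 patients for each group". It does not call TNF-α the primary outcome.

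Statistical analysis plans ANOVA and ANCOVA across the four groups. The one multiplicity rule in the article is: "Bonferroni will be used to pairwise comparisons for the values after the intervention".

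**The concern.** Two separate problems follow from the unranked list.

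First, nothing in the article says which outcome decides the trial. Bonferroni over pairs of groups limits error within one outcome and does nothing across outcomes. If the result to be presented as primary can be chosen after the data are seen, the 5% in the sample size section does not describe the risk of a false claim. The 90% power belongs to TNF-α, which the objectives do not single out.

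Second, 25(OH)D stands level with the efficacy outcomes. Patients enter below 30 ng/ml and unsupplemented, two of the four groups receive vitamin D, and patients under 90% compliance are excluded. A difference in 25(OH)D would show that the product was taken and absorbed. The protocol itself treats its change as an explanatory variable in the second objective, and the title, the abstract and the aim at the end of the Background leave it out of the outcomes of interest. Reported as a positive primary result, it would say nothing about benefit.

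**Working it through.** **Sample size.** The 20 per group cannot be reproduced, because no difference or set of group means is stated. With SD 1.25, α 0.05 and 90% power, 20 per group corresponds to:

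- a TNF-α difference of 1.28 between two means, from 1.25 × √(2/20) × (1.960 + 1.282);
- a largest difference of 1.53 in a four-group ANOVA with the other two means midway.

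The figure is plausible but cannot be verified. The attrition step is consistent with a 20% loss: 20/(1 − 0.20) = 25, and 4 × 25 = 100. All of this concerns TNF-α only.

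**Counting outcomes other than 25(OH)D.** Four cytokines, CRP/albumin, CEA and BMI make 7. Body composition adds 1 or 2: if body fat and fat-free mass are both percentages they sum to 100 and give the same test. CRP adds 0 or 1, depending on whether it counts as an inflammatory biomarker apart from the ratio. The total is 8 to 10.

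**False positives across outcomes.** Assume no effect on any of these, each outcome held at 5% overall (which credits the planned Bonferroni over pairs), and any one significant outcome reportable as the primary result. For k independent outcomes the chance of at least one false positive is 1 − 0.95^k:

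| k | 1 − 0.95^k |
|---|---|
| 8 | 34% |
| 9 | 37% |
| 10 | 40% |

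Independence is unrealistic. Simulating 10 equally correlated outcomes (four groups of 20, F test at 0.05, 40,000 replicates) gave:

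| Correlation | At least one false positive |
|---|---|
| 0.3 | 36% |
| 0.5 | 30% |
| 0.7 | 22% |

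A more structured assumption gave 31%: inflammatory markers correlated 0.5, CRP and its ratio 0.95, CEA independent, BMI correlated 0.6 with body fat, and fat and fat-free mass near mirror images.

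**Cost of correcting all of them instead.** Dividing 0.05 over 11 (the ten plus 25(OH)D) gives 0.0045 each. At 20 per group, TNF-α power falls from 90% to about 64% (ANOVA) or 66% (two means). Restoring 90% needs about 31 to 33 evaluable patients per group.

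**25(OH)D.** The documents give no expected rise and no SD, so both are assumed. Power for 20 versus 20 at two-sided 5% is Φ(d/(SD × √(2/20)) − 1.96). For d = 10 and SD 10, this is Φ(3.16 − 1.96) = Φ(1.20) = 89%.

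| Assumed difference | SD 6 | SD 8 | SD 10 |
|---|---|---|---|
| 5 ng/ml | 75% | 51% | 35% |
| 10 ng/ml | 100% | 98% | 89% |
| 15 ng/ml | 100% | 100% | 99.7% |

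At α = 0.05/6, the level for one of six Bonferroni-corrected pairs, the 10 ng/ml row becomes 99.6%, 91% and 70%.

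**The case against.** The strongest reply is that the article states a primary objective, not a success rule. It nowhere says that one significant variable makes the trial positive, so a reader who infers that any significant result will be claimed goes beyond the text. That stands, and the error rates are therefore conditional. The text does not exclude such a claim either, and an unranked primary tier leaves it open.

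A second reply is that a journal article is condensed, and that rules across outcomes may sit in a full protocol or analysis plan that is not shown. That is fair for the correction method, and its absence alone would be no finding. It does not remove what this article does state: an unranked primary list, beside a sample size built on one member that is not named as primary.

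Three stronger readings are tempting and should not be drawn:

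- A reader might count 11 null outcomes and quote 1 − 0.95^11 = 43%. That treats 25(OH)D as unaffected by vitamin D, counts CRP apart from its ratio, and counts fat and fat-free mass as independent.
- A reader might count 11 × 6 = 66 unprotected pairwise tests. The planned Bonferroni already covers the six pairs within each outcome.
- A reader might call a 25(OH)D result certain, or a false positive. The size of the rise is an assumption, and a difference would be a true effect.

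It can also be said that powering on TNF-α alone is openly stated and claims nothing for the other variables. That is correct; the defect is that the objectives do not give TNF-α the same standing.

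Finally, the remedy demotes domains that the title names, and a two-group contrast uses half of a factorial trial. Both are real costs.

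**Conclusion.** The point holds. The primary objective contains about 8 to 10 outcomes besides 25(OH)D with no ranking, the sample size supports only TNF-α, and the stated correction works within outcomes only.

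If any one significant outcome may be reported as the primary result, the false-positive risk is 34% to 40% for 8 to 10 independent outcomes, and about 22% to 36% for 10 outcomes at correlations of 0.7 to 0.3. Every case examined is at least four times the stated 5%, so the conclusion does not hinge on the exact count or correlation. It does hinge on that reading of success, which the article leaves open rather than adopts.

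The 25(OH)D problem is separate and is not a type I error. A difference there is likely under an assumed 10 ng/ml or more, and far from assured at 5 ng/ml. In either case it would show uptake, not benefit.

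**What to change.** Amend the objectives before unblinding, and record the date of the change:

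- **Primary:** TNF-α at week 8, co-supplementation versus double placebo, the outcome and contrast on which the sample size is based. One outcome and one contrast need no split of α and keep the planned 20 evaluable patients per group.
- **Secondary:** the other inflammatory markers (stating whether CRP is one of them), CRP/albumin, CEA, BMI and body composition, either with Holm correction or explicitly without confirmatory claims.
- **Exposure/adherence:** serum 25(OH)D, reported as such.

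The record of the date matters. The Trial status section gives recruitment completion as 5/15/2019 while describing the trial as enrolling, and the article appeared in December 2019. A late, undated change of primary outcome would raise its own doubts.

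No patients or measurements are added. The cost is in claims: CEA and nutritional status can no longer carry an unadjusted confirmatory claim, and the primary contrast compares only two of the four groups directly, 50 of the 100 patients recruited. Correcting across all outcomes instead would keep them level but, over 11 outcomes, would need about 31 to 33 evaluable patients per group.

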### Participants

Participants will comprise 100 patients with stage II or III CRC. The inclusion criteria will consist of: patients with stage II or III CRC if they have to begin chemotherapy; aged > 18 years; BMI range of 18.5–30 kg/m^2^; serum 25(OH)D < 30 ng/ml; not having autoimmune disease, diabetes, hypertension, or renal, hepatic, parathyroid, and gastrointestinal disorders; not taking vitamin D and/or omeaga-3 supplements and other vitamin/mineral supplements or parenteral nutrition; not taking laxative and/or anti-inflammatory medications; not allergic to fish and fish products; and without history of having other cancers. Exclusion criteria will consist of: affected by any acute disease during the study; changes to the chemotherapy plan; refusal to continue with chemotherapy; unwilling to continue the study; also, we will exclude patients who were less than 90% compliant with treatment.

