### Randomization and blinding

The randomization assignment will be performed using computer-generated random numbers. The 100 participants who meet the criteria will be randomly allocated into four groups: 1) a 50,000 IU vitamin D soft gel (weekly) plus 2 omega-3 fatty acid capsules (daily), each capsule containing 330 mg omega-3 fatty acid; 2) a 50,000 IU vitamin D soft gel (weekly) plus 2 omega-3 fatty acid placebo (daily); 3) a vitamin D placebo (weekly) plus 2 omega-3 fatty acid capsules (each capsule containing 330 mg omega-3 fatty acid); and 4) a vitamin D placebo (weekly) plus 2 omega-3 fatty acid placebo (daily). Each omega-3 fatty acid capsule (MorDHA VISION, Minami Nutrition, Belgium) contains 54 mg EPA, 250 mg DHA, and 26 mg of other omega-3 fatty acids. The 50,000 IU vitamin D soft gels are supplied by Zahravi, Iran. The vitamin D and omega-3 fatty acid placebo contain oral paraffin and corn oil, respectively, are supplied by Zahravi, Iran, and are carefully matched in appearance with vitamin D and omega-3 fatty acid soft gels. Patients will receive verbal and written counseling on how to consume the capsules. Compliance will be evaluated by capsule count every 2 weeks. The supplementation will begin before the first session of chemotherapy.

For blinding, a person not involved in the study protocol will create the randomization list, assigning participants to the vitamin D, omega-3, co-supplementation, or placebo group. Vitamin D, omega-3, and placebo tablets will be placed into unlabeled identical containers. The study leader will label these containers with participant numbers using the randomization list. All investigators and participants will be blinded to the random assignments.

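### Five post-randomisation events remove patients, so the groups compared at the end are not the randomised groups

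*Protocol article*

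**What the plan says.** The protocol article, Participants, gives these exclusion criteria: "affected by any acute disease during the study; changes to the chemotherapy plan; refusal to continue with chemotherapy; unwilling to continue the study". It then adds: "we will exclude patients who were less than 90% compliant with treatment".

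Randomization and blinding places allocation earlier: "The 100 participants who meet the criteria will be randomly allocated into four groups". Intake is checked during treatment: "Compliance will be evaluated by capsule count every 2 weeks". Each arm takes one soft gel a week and two capsules a day, active or matched placebo.

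Sample size arrives at 20 per group and then adds a margin: "To allow for attrition, 25 patients will be recruited for each group". It gives no expected loss rate and does not say whether the margin covers the exclusions.

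Statistical analysis compares the four groups at the end of the study by ANCOVA, adjusted for baseline and covariates. It does not say that excluded patients stay in that comparison.

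**The concern.** Entry criteria applied before allocation do no harm to a randomised comparison. These five act after it. A patient who falls acutely ill, has chemotherapy altered or refused, gives up the study, or misses capsules during chemotherapy may well differ in inflammatory state from one who does none of these. The outcomes include TNF-α, interleukins, CRP/albumin, CEA and body composition, so the reason for removal can be tied to what is measured.

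Allocation may matter too. The Background cites animal work in which omega-3 lessened the side effects of cancer or its treatment. If that carried over to patients, removal rates could differ by arm. The retained groups would then differ for reasons other than the supplements. Recruiting more patients would not cure this, and a sample never taken from a removed patient cannot be recovered later.

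A smaller concern is that the 90% threshold can be read in two ways that produce quite different analysis sets.

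**Working it through.** **1. The plan's own figures.** The allowance is 5 of 25 = 20%. The inflation is correct: 20/(1 − 0.20) = 25, and 4 × 25 = 100. The 20 itself comes from "considering sigma (standard deviation of TNF-α) of 1.25, 90% power, α of 0.05, resulting in 20 patients for each group". It cannot be reproduced, because the TNF-α difference is not stated. In a four-group ANOVA with the other two means midway, 20 per group at 90% power corresponds to a maximum difference of about 1.22 SD (1.22 × 1.25 ≈ 1.53 units).

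**2. Order of events.** Allocation comes first. Supplementation starts before the first chemotherapy session, and capsule counts follow every two weeks. Low compliance, refusal to continue chemotherapy and illness during the study therefore come after randomisation, as in practice do plan changes and withdrawal.

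**3. Size of the selection bias.** Assumptions, none of them from the article: the patients most prone to exclusion are removed, exclusion propensity and outcome are bivariate normal with correlation ρ, a fraction q is removed, and treatment has no effect. The mean outcome of those retained shifts by −ρ·φ(z)/(1 − q), in SD units, where z is the upper-q normal quantile.

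- q = 0.10: φ(1.282)/0.90 = 0.1755/0.90 = 0.195
- q = 0.15: φ(1.036)/0.85 = 0.2332/0.85 = 0.274
- q = 0.30: φ(0.524)/0.70 = 0.3477/0.70 = 0.497

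| Exclusion in two arms | Gap before ρ | ρ = 0.3 | ρ = 0.5 |
|---|---|---|---|
| 15% v 30% | 0.222 | 0.07 SD | 0.11 SD |
| 10% v 30% | 0.302 | 0.09 SD | 0.15 SD |

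With the SD of 1.25, the range 0.07–0.15 SD is about 0.09–0.19 TNF-α units. Under these assumptions, equal exclusion rates give no shift.

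**4. The 90% rule.** Over 8 weeks there are 8 soft gels and 2 × 7 × 8 = 112 capsules, 120 in all.

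- By product: 90% of 8 is 7.2, so all 8 soft gels are needed. One missed gives 7/8 = 87.5%, and the patient is excluded.
- Pooled: 90% of 120 is 108. A patient who took none of the 8 soft gels scores 112/120 = 93.3% and is kept.

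**5. Losses against the allowance.** With assumed independent loss rates, a given group of 25 ends below 20 with probability 0.03 at 10% loss, 0.38 at 20% and 0.81 at 30%. At the 1.22 SD difference, power is 0.90 with 20 per group, 0.81 with 16, 0.78 with 15, and 0.96 with all 25.

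**The case against.** The strongest reply is that this is a condensed article with no SAP at hand, and that analysis populations are commonly left to the SAP. The word exclude could mean removal from treatment, from follow-up or from one analysis set. That stands against one tempting inference, that the trial will have no all-randomised analysis of any kind; silence does not show that. It does not remove the point. The article states an explicit exclusion rule, and nothing in Sample size, Randomization and blinding or Statistical analysis keeps these patients in the comparison.

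The bias may also be small. Every arm has the same capsule burden with matched placebos and blinding, so neither burden nor knowledge of allocation should drive unequal loss. Adjustment for baseline removes part of any selection acting through baseline inflammation. Even 0.15 SD is under half the standard error of a two-group difference at 20 per group, √(2/20) = 0.32 SD. The one treatment-related mechanism the Background offers would remove more sick patients from the placebo arm and so pull the result towards no effect. All of this is fair, and it is why the size is called modest and no direction is claimed.

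A reader might also infer that the trial will fall below 20 per group. The article gives no loss or miss rate, so a shortfall is possible but not demonstrated. Nor is the 90% threshold an arithmetic error: the two counts in the working show only that the rule is ambiguous.

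**Conclusion.** The point holds as a flaw in a stated rule. Followed as written, the plan compares subsets selected by compliance and clinical course, so randomisation no longer fully protects the comparison. In the illustration the bias is 0.07–0.15 SD. That rests on assumed exclusion of 10–15% against 30%, an assumed correlation of 0.3–0.5, and no credit for baseline adjustment. The true size and direction could not be recovered from the retained patients alone.

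The compliance count is a secondary point of wording. Loss of power is a possibility that depends on rates the article does not give. It would be moderate, about 0.81 with 16 per group, at a difference that is itself back-solved and not stated.

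**What to change.** - Make the primary analysis all randomised patients, in the group to which they were allocated.
- Record the five events as protocol deviations or intercurrent events, not as removals from the analysis.
- Take the planned end-of-intervention sample from these patients where they consent. Some who are unwilling to continue will decline.
- State a method for outcomes that are still missing, for example baseline-adjusted multiple imputation with a sensitivity analysis.
- Keep the set with at least 90% compliance as a supportive per-protocol analysis, with compliance counted separately for each product (for vitamin D, soft gels taken out of 8).

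The cost is wording, a visit that is already planned, and the missing-data work. Non-compliance may dilute the estimate slightly. Timing matters: Trial status puts the end of recruitment at 5/15/2019, and eight weeks later is 10 July 2019, before the article's publication date of 2019-12-09. If follow-up is already complete, apply the change to all patients with available samples. The change concerns the analysis set only and sets no rule on when treatment stops.
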